**Figure 1 F1:**
[figure not shown]
**Flow-chart of the study**.

### Intervention

Patients randomized to the intervention group will participate once in a GMC instead of a standard individual visit. The GMC will provide individual medical visits conducted within a group, giving patients the opportunity to spend more time with their own clinician in the setting of a support group. In this way patients can learn from other patient's experiences with similar topics. A social worker will be present during every GMC. Besides leading the discussion and making sure every patient receives equal attention from the clinician, the social worker will be available for psychosocial related questions and support. The group visit itself will take 90 minutes. In advance, half an hour will be scheduled for physical examination, where privacy concerns will be taken into account. The control group will have their usual individual visit with the clinician. The clinician and the social worker will both use protocols with information based on most up-to-date publications concerning *BRCA *gene mutation related topics, specially developed for the GMCs.

### Study outcomes

At baseline, 1 week after and 3 months after the (group or individual) visit participants will be asked to fill out a questionnaire. Patients refusing participation will be asked to fill out one questionnaire to gain insight in reasons for not participating. Demographical data will be collected as well as the following measures.

### Primary outcome measures

Empowerment is the first primary outcome, which will be measured using the Empowerment Questionnaire for breast cancer patients. This questionnaire has been developed and validated in the Netherlands for the assessment of empowerment in psychiatric patients. With minor revisions, the 40-item questionnaire was validated in breast cancer survivors. The study involved 140 non-metastatic breast cancer patients who were treated in the past with curative intent. Four factors were extracted, explaining 53 percent of the total variance. Factor 1 was labeled 'Personal Strength', factor 2 'Social support', factor 3 'Community' and at least factor 4 'Health Care'. The internal consistency reliability for each factor demonstrated good reliability for all four factors and for the total empowerment scale (alpha = .94)[48].

Another primary outcome is psychological distress measured by the Symptom Checklist-90 (SCL-90). SCL-90 is designed to evaluate a broad range of psychological problems and symptoms of psychopathology. It can be used for measuring the progress and outcome of psychiatric and psychological treatments [45,49]. It consists of 90 items, yielding nine scores along primary symptom dimensions and three scores among global distress indices. A countless number of studies demonstrated the reliability, validity and utility of the instrument.

### Secondary outcome measures

Besides the primary outcomes, the following secondary outcomes are measured. The Cancer Worry Scale will be used to assess the fear of cancer. It consists of 8 items and is used in several studies among cancer patients. The internal consistency is good (alpha = .80)[50,51].

The information needs before the consultation and the actually received information after the consultation will be measured by a list of relevant topics for BRCA mutation carriers, including topics like prophylactic mastectomy, use of oral contraceptives, depressed mood. Participants can also add their own topics. In advance of the visit participant are asked to fill out which topics they want to discuss during the consultation. One week after the visit participants will indicate on the topic list which topics have actually been discussed.

Self-examination of the breasts will be measured by a question about the frequency of self-examination and about the reason not to examine their own breasts. One question is included to assess the patient's choice for a prophylactic mastectomy or surveillance.

To assess the patient satisfaction a combination of the QUOTE questionnaire [52] and some GMC specific questions will be used [34]. Overall satisfaction with the visit will be rated on a scale from 1 (not satisfied at all) to 5 (very satisfied).

The quality of life will be measured by the EORTC-Q30 and the EORTC-BR23. The EORTC-Q30 is a health-related quality of life questionnaire which is validated for oncological clinical research [53]. Chronbach's alpha was close to or higher than 0.70 for seven of the nine scales and ranged between 0.19-0.92 [54]. The questionnaire consists of 30 items, including a functional, symptom and health-related quality of life subscale. The EORTC-BR23 is a validated breast cancer-specific questionnaire [55,56]. The questionnaire consists of 23 items, including side effects of therapy, body image, sexuality and outlook for the future.

To evaluate the cost-effectiveness of the intervention costs will be measured by several questions from the Trimbos/iMTA questionnaire for Costs associated with Psychiatric Illness (TiC-P). This is a frequently used instrument for economic evaluations in mental health care [57].

The researcher will be present during the GMC for measuring the time spend per patient. This measure will be used in the analyses to test the relation between time spend per patient and the effectiveness of the GMC. Besides, topics discussed during the visits will be measured by the researcher.

### Power calculations

The primary aim of GMCs is to increase patient empowerment and to prevent an increase of psychological distress. Data on these outcome measures for *BRCA *mutation carriers are not yet available, therefore data from a rather comparable population, breast cancer patients, is used for the power analysis. Also, data of the SCL-90 is more widespread compared to empowerment data for breast cancer patients, therefore results of this questionnaire have been used. A healthy score on the SCL-90 ranges between 90-130, while breast cancer patients, one year or longer after curative treatment for breast cancer, achieved an average score of 138.5 [58]. In this study we strive for a high normal average score of 125. This implies that an average difference of 13.5 points can be defined as clinically relevant. The standard deviation is 45, which is based on three norm groups [49]. To assess a clinically relevant effect of GMC on psychological distress with a power of 80%, a two-side significance of 5%, a standard deviation of 45 and an expected drop-out of 15%, 80 patients need to be included in each group.

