**Methods/design:**

In this randomized controlled trial, 160 BRCA mutation carriers diagnosed maximally 2 years ago are recruited from the Radboud University Nijmegen Medical Centre. Participants are randomized in a 1:1 ratio to either the GMC intervention group (onetime participation in a GMC instead of a standard individual visit) or to a usual care control group. Primary outcome measures are empowerment and psychological distress (SCL 90). Secondary outcome measures are fear of cancer, information needs before the consultation and the received information, self-examination of the breasts, patient satisfaction, quality of life and cost-effectiveness. Data are collected via self-reported questionnaires 1 week before the visit, and at 1 week and at 3 months follow-up. A pilot study was conducted to test all procedures and questionnaires.

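### The inputs printed in the power paragraph do not give 80 women per group: unadjusted they need about 207, and 80 fits the planned ANCOVA only with an unstated correlation of about 0.78

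*Protocol article*

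**What the plan says.** The section on power calculations in the protocol article bases the sample size on the SCL-90. It takes a mean of 138.5 in treated breast cancer patients, aims for 125, and concludes: "This implies that an average difference of 13.5 points can be defined as clinically relevant". On variability it says: "The standard deviation is 45, which is based on three norm groups". With 80% power and a two-sided 5% level it then arrives at "a standard deviation of 45 and an expected drop-out of 15%, 80 patients need to be included in each group".

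The abstract carries the same total ("160 BRCA mutation carriers diagnosed maximally 2 years ago are recruited") and equal allocation ("Participants are randomized in a 1:1 ratio").

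The statistical analysis section makes the primary analysis an ANCOVA with group as the factor and, for the SCL-90, the baseline score as covariate. Neither section gives a baseline to follow-up correlation, a residual SD or an SD of change.

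**The concern.** The power paragraph lists the difference, SD, power, significance level, sidedness and drop-out, then presents 80 per group as the result. A reader can therefore check it directly, and it fails: a standardised difference of 0.30 needs far more than 68 evaluable women per arm at 80% power. The SD of 45 is described as coming from norm groups, so it reads as the spread of scores between people, not as a residual SD after baseline adjustment.

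At stake is whether the trial can detect the difference that the article itself calls clinically relevant. If the 80% is unsupported, readers will overrate how informative the distress comparison is.

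**Working it through.** **Inputs** (power calculations section unless noted)
- Difference: 138.5 − 125 = 13.5 points
- SD: 45
- Two-sided significance level 5%, power 80%
- Drop-out 15%, so 80 enrolled leaves 80 × 0.85 = 68 evaluable per arm
- Allocation 1:1 (abstract)
- Primary analysis: ANCOVA with baseline SCL-90 as covariate (statistical analysis section)
- Correlation r between baseline and follow-up: not given, so varied below as an assumption

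**Step 1. Try to reproduce the stated 80, unadjusted.**
n per arm = 2 × (1.960 + 0.842)² × (45/13.5)² = 174.4; the t-test version gives 175.4.
With drop-out: 175.4/0.85 = 206.3, so 207 enrolled per arm. Depending on rounding and on normal or t quantiles, the figure is 206 to 208.
The stated 80 is not reproduced. The ratio is 207/80, about 2.6.

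**Step 2. Other routes to 80.**
- One-sided 5%: 138 evaluable, 163 enrolled per arm.
- Drop-out applied as n × (1 + 0.15) instead of n/(1 − 0.15): 202 per arm.
- Two-sided per-arm number misread as the total: 175/2 = 87.5, about 103 per arm after drop-out. A two-sided one-sample formula also gives about 103.
- One-sided one-sample formula: 68.7/0.85 = 80.8, about 81. This is close, but it contradicts the stated two-sided test and two-group design.
- ANCOVA with a high, unstated correlation (step 4).

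**Step 3. What 80 per arm delivers, unadjusted.**
At 68 evaluable per arm and standardised difference 0.30, t-test power is 41%. With no drop-out at all (80 evaluable) it is 47%.
The standardised difference detectable with 80% power at 68 per arm is 0.484, and 0.484 × 45 = 21.8 points.

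**Step 4. What 80 per arm delivers under the planned ANCOVA.**
Residual SD = 45 × √(1 − r²). Power is for 13.5 points with 68 evaluable per arm; detectable difference = 0.484 × residual SD.

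| r (assumed) | Residual SD | Power | Detectable difference at 80% power |
|---|---|---|---|
| 0 | 45.0 | 41% | 21.8 |
| 0.5 | 39.0 | 52% | 18.9 |
| 0.6 | 36.0 | 58% | 17.4 |
| 0.7 | 32.1 | 68% | 15.6 |
| 0.78 | 28.2 | 79% | 13.6 |

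The correlation at which 68 per arm reaches 80% power: residual SD = 13.5/0.484 = 27.9, so r = √(1 − (27.9/45)²) = 0.78. The normal approximation agrees: √(1 − 68/174.4) = 0.78.

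**The case against.** The strongest objection is that the trial will not be analysed by an unadjusted comparison. The planned ANCOVA removes variance explained by the baseline score, and the abstract places the baseline questionnaire one week before the visit and the first follow-up one week after it. Over about two weeks a correlation near zero should not be the headline assumption. This stands. A reader might infer that the planned trial has 41% power, or that it would miss a true 13.5-point effect more often than it found it. The documents support neither. The 41% is the value at r = 0, and power falls below one half only if r is below about 0.47. Likewise 207 per arm is the unadjusted requirement, not what the planned analysis needs at every r.

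It can also be said that a journal article condenses a fuller protocol, where a correlation may be recorded. A missing correlation alone would be a weak complaint. But the paragraph presents 80 as the consequence of the inputs it lists, and it is not. That is a misstatement in the printed text, whatever the fuller document holds.

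The source of the 80 cannot be inferred. A slip in the formula and an unprinted correlation both come close, so the figure should not be attributed to either.

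Two further readings go too far. The absence of a separate calculation for empowerment is not part of this error: the article says that SCL-90 data were chosen because they were more widely available. Nor does the article say that a non-significant distress result would be taken as showing no relevant effect.

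**Conclusion.** The power statement is wrong as written and must be corrected. On the printed inputs, 80% power needs about 175 evaluable or 207 enrolled women per arm without baseline adjustment. The stated 80 per arm gives about 41% power on that basis.

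For the analysis actually planned, the document does not determine the power. It is 52% to 68% for correlations of 0.5 to 0.7, and it reaches about 80% only near 0.78. Those correlations are assumptions shown as a range; none comes from the document. The figures also assume 15% drop-out in both arms, an SD of 45 that describes raw scores, and independent observations. The mismatch between inputs and result is certain; the size of any shortfall under ANCOVA is not.

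**What to change.** Correct the power paragraph so that the stated power matches the stated inputs, in one of two ways:

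1. If no adjustment was assumed, report that 80 per arm (68 evaluable) with SD 45 gives about 41% power for 13.5 points unadjusted, with a detectable difference of 21.8 points at 80% power. Note that the planned ANCOVA will do better by an amount that depends on the correlation.
2. If the calculation assumed ANCOVA, state the correlation actually used, with a source independent of the sample size, and show power at lower values such as 0.5, 0.6 and 0.7. The value 0.78 should not be inserted merely because it returns 80.

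The change is to wording only. It requires no extra patients and no change to the design or analysis. The price is a stated power that is less favourable, or explicitly conditional on a correlation.

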### Statistical analysis

For the primary analysis a covariance analysis (ANCOVA) will be conducted. Differences in empowerment and SCL-90 scores (primary outcome measures) at baseline and one week after the GMC between the intervention group and control group will be compared. In addition ANCOVA provides the opportunity to compare trends over time between the two groups. The SCL-90 scores at T1 or T2 will be included as dependent variables and the group (individual consult or GMC) as independent variable. Furthermore, the SCL-90 score at baseline will be a covariate. The analysis of the secondary outcome measures is a repeated measurement analysis (ANOVA or mixed model) to compare trends over time between the two groups.

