To fulfill the needs just mentioned concerning psychosocial support and information we have introduced group medical consultations (GMCs) for the surveillance of *BRCA *mutation carriers. A GMC provides individual medical visits conducted within a group, giving patients the opportunity to spend more time with their own clinician in the setting of a support group with a behavioral health professional and learn from other patients experiencing similar topics. In contrast to the typical 15-20-minute office visit, a 90-minute group-visit with 8-12 patients permits ample time for discussion and education. The incorporation of the individual medical visit in a GMC distinguishes GMCs from educational workshops and support- and self-management groups. In general, the group of patients in a GMC is composed of different participants from meeting to meeting. Currently, GMCs have been offered to patients of different ages with a variety of diseases [27,28]. Although several benefits of GMCs compared to individual visits have been reported, the effects have not been evaluated for the surveillance of *BRCA *mutation carriers.

Most previous studies showed improved satisfaction in patients receiving GMCs and in health professionals providing GMCs. The unhurriedness of the clinician and the time spent with the clinician is appreciated most by patients [29-33]. Clinicians were positive about the innovative and multidisciplinary working method [34]. Besides improved quality of life, which is reported in several studies [32,35,36], also improved health behavior, self-efficacy for following certain health promoting interventions and knowledge of the disease was shown among diabetes patients and patients with coronary artery disease who participated in a group visit [35,37]. Also, quality of care is improved. For example, in a study of diabetic patients group visit participation was positively associated with patients receiving preventive procedures, review of medication and microalbuminuria test recorded in the registry [38]. Other studies in diabetic patients have confirmed these results [31,39-41]. When planned carefully, this type of visits may increase clinician satisfaction and productivity [30,36,42-44].

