### Recruitment and randomization

Women with the *BRCA *mutation having their yearly surveillance in the Radboud University Nijmegen Medical Centre will be informed about the study during an individual visit to the outpatient clinic or approached via a telephone call by the researcher. As shown in Figure 1 patients will be randomized for their next visit to either the intervention group (GMC) or the control group (individual visit) after informed consent is obtained. Randomization will take place per patient in a 1:1 ration and in blocks of 16 patients. The individual clinician, will meet the same number of patients in a GMC and in an individual consultation, therefore we pre-stratified for clinician.

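### The primary ANCOVA ignores the shared GMC sessions, so if outcomes correlate within a session its standard errors are too small and its type I error exceeds 5%

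*Protocol article*

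**What the plan says.** All places are in the protocol article.

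- **Analysis (Statistical analysis).** "For the primary analysis a covariance analysis (ANCOVA) will be conducted". Both primary outcomes are named. The terms are spelled out for the SCL-90: the score at T1 or T2 is the dependent variable, with "the group (individual consult or GMC) as independent variable", and "the SCL-90 score at baseline will be a covariate". No session effect or cluster-robust variance is mentioned. A mixed model appears only for the secondary outcomes, as an alternative to ANOVA.
- **Delivery (Background; Intervention).** The article describes how "a 90-minute group-visit with 8-12 patients permits ample time for discussion and education". "Patients randomized to the intervention group will participate once in a GMC instead of a standard individual visit". By contrast, "The control group will have their usual individual visit with the clinician".
- **Allocation (Recruitment and randomization).** "Randomization will take place per patient in a 1:1 ration and in blocks of 16 patients". The individual clinician sees equal numbers in both arms, and "therefore we pre-stratified for clinician". Clinician is not among the stated model terms.
- **Sample size (Power calculations).** 80 per arm, from a difference of 13.5 points, SD 45, 80% power, two-sided 5% and 15% dropout. No ICC or design effect is given.
- **Mechanism (Background; Intervention; Discussion).** Women are meant to learn from one another, contact with other carriers is presented as the distinctive feature, and in an earlier group programme events in some members are thought to have affected others.

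**The concern.** This is a partially nested design: randomisation is by woman, treatment is by session in one arm, and there is no grouping by session in the other. Women in the same session share its composition, its atmosphere, the topics raised and whatever other members report. Any such shared influence makes their outcomes alike. The GMC arm mean then carries less information than the same number of independent women would give.

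An ANCOVA on arm and baseline counts every woman as independent. Adjusting for baseline does not help, because session effects arise after baseline. It removes variance between women but leaves the session variance in place, so the ICC of the adjusted outcome is higher than the raw one.

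At stake are the width of the intervals and the false-positive rate for both primary outcomes. The Discussion ties a recommendation for regular care to this result, and the error runs towards declaring a difference.

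**Working it through.** **Inputs from the article.** Sessions of 8-12 women, one session each; 80 per arm; 15% dropout; two-sided 5%. Hence 80/12 = 6.7 to 80/8 = 10, about 7-10 sessions. Completers per session: 8 × 0.85 = 6.8 to 12 × 0.85 = 10.2.

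**Assumed input.** The ICC ρ of the baseline-adjusted outcome within a session, shown at 0.01, 0.02, 0.05 and 0.10.

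**The plan's own figure.** The usual two-sample formula with the stated inputs gives 2 × (1.960 + 0.842)² × 45² / 13.5² = 174.4, so 175 per arm, and 175/0.85 = 206 after dropout. The stated 80 per arm does not reproduce. That is a separate matter. What counts here is that no stated input allows for clustering.

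**Variance.** With n analysed per arm and m completers per session:

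- model's variance of the arm difference: 2σ²/n
- true variance: σ²/n + σ²[1 + (m − 1)ρ]/n
- ratio: f = 1 + (m − 1)ρ/2

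The standard error is too small by a factor √f, and the actual two-sided level is 2[1 − Φ(1.96/√f)].

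Example, m = 10.2 and ρ = 0.05: f = 1 + 9.2 × 0.05/2 = 1.23; 1.96/√1.23 = 1.767; level 7.7%.

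| ICC (assumed) | f, m = 6.8 | level | f, m = 10.2 | level |
|---|---|---|---|---|
| 0 | 1.00 | 5.0% | 1.00 | 5.0% |
| 0.01 | 1.029 | 5.3% | 1.046 | 5.5% |
| 0.02 | 1.058 | 5.7% | 1.092 | 6.1% |
| 0.05 | 1.145 | 6.7% | 1.23 | 7.7% |
| 0.10 | 1.29 | 8.4% | 1.46 | 10.5% |

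**Simulation of the stated ANCOVA** (10,000 runs per setting; baseline correlation 0.78, an assumption). Levels at ICC 0, 0.01, 0.05 and 0.10:

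- 10 sessions of 7 analysed women: 5.0%, 5.4%, 6.6%, 8.2%
- 7 sessions of 10: 4.9%, 5.5%, 7.8%, 10.0%

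These agree with the formula.

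**Raw against adjusted ICC.** If the session effect is unrelated to baseline, the adjusted ICC is the raw one divided by (1 − r²). A raw 0.02 becomes 0.02/0.75 = 0.027 at r = 0.5, or 0.02/0.392 = 0.051 at r = 0.78 (both r assumed).

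**Omitted clinician.** Stratifying by clinician and then leaving clinician out of the model makes the standard error too large, which works the other way. With 8 sessions of 8, four clinicians and a clinician ICC of 0.05 (all assumed), the simulated level was 5.0%, 6.8% and 8.4% at session ICC 0.01, 0.05 and 0.10. Without a clinician effect it was 5.6%, 7.2% and 9.0%.

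**The case against.** The strongest reply has five parts.

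1. **No ICC is given.** A reader might infer that the type I error certainly exceeds 5%, or that it reaches the top of the range. The documents do not support that. Exposure is a single 90-minute session, and at ICC 0.01 the excess is slight. Blocks of 16 at 1:1 give 8 GMC women per block, which points towards smaller sessions, though 8-12 is what is stated. This part stands, and the conclusion has to be conditional.
2. **If the GMC affects nobody, sharing a session creates no correlation.** True. The inflation concerns the null of no average effect. That null is relevant here, because the Abstract and Background foresee that some women may be helped and others made more fearful. Where sessions differ, intervals are too narrow whether or not the average effect is zero.
3. **Omitting the clinician offsets it.** Partly. Under the assumptions above it cancels the excess at a session ICC of 0.01 but not at 0.05 or 0.10.
4. **An unseen analysis plan may add a session term.** Possible. But the article does state its model terms, and its sample size makes no allowance either. The point is about the rule as stated.
5. **The secondary analyses may be sound.** A reader might extend the fault to every secondary comparison. The article leaves ANOVA or a mixed model open there and does not fix the random effects, so that cannot be concluded.

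**Conclusion.** The concern holds in conditional form. The stated primary model treats women as independent although one arm is nested in about 7-10 shared sessions. If within-session correlation is positive, its standard errors are too small and the level for no average effect is above 5%.

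Under the assumed ICCs, 15% dropout and the normal approximation, the true variance exceeds the model's by 3-5% at ICC 0.01, 6-9% at 0.02, 15-23% at 0.05 and 29-46% at 0.10. The effect therefore runs from negligible to roughly a doubling of the nominal level. The direction follows from the design; the size cannot be fixed from the documents. Omission of the clinician reduces the excess somewhat.

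**What to change.** For both primary outcomes, replace the ANCOVA with a partially nested linear mixed model:

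- fixed effects for arm, baseline score and clinician (the stratifier);
- a random intercept for GMC session in the GMC arm only, each control being her own unit;
- residual variance allowed to differ by arm;
- Satterthwaite or Kenward-Roger degrees of freedom.

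The clinician and session terms belong together: adding clinician alone would remove the offset and leave the inflation exposed.

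Record the session identifier for every GMC participant and report the estimated ICC. Include the same session term in whichever secondary model is used. State in Power calculations that 80 per arm makes no allowance for clustering.

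Cost: revised analysis wording and one extra data field. Recording it should be easy, since the researcher attends the sessions, whereas without it the correction cannot be made later. Intervals will be wider with fewer degrees of freedom, and power will be lower than an analysis assuming independence suggests. With only 7-10 sessions the session variance will be imprecisely estimated, so the reported ICC needs its interval.

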## Abstract

**Background:**

*BRCA *mutation carriers have a 40-80% life-time risk of developing breast cancer. They may opt for yearly breast cancer surveillance or for prophylactic mastectomy. Both options show increased survival rates. It is a complex choice to be made between these two options. As a result most women experience high levels of distress and high needs for information. To fulfill the needs for psychosocial support and information we have introduced group medical consultations (GMCs). A GMC provides individual medical visits conducted within a group. This 90 minute group-visit with 8-12 patients gives patients the opportunity to spend more time with their clinician and a behavioral health professional and learn from other patients experiencing similar topics. However, it should be noted that group sessions may increase fear in some patients or influence their decision making.

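### For the secondary scales the plan permits a three-wave repeated-measures ANOVA with no stated baseline covariate, an option that would lose precision which baseline adjustment keeps

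*Protocol article*

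**What the plan says.** The Statistical analysis section of the protocol article describes two approaches. The primary analysis is an ANCOVA with the follow-up SCL-90 score as dependent variable and group as independent variable, and it states how baseline enters: "Furthermore, the SCL-90 score at baseline will be a covariate". The secondary outcomes then get a different description: "The analysis of the secondary outcome measures is a repeated measurement analysis (ANOVA or mixed model) to compare trends over time between the two groups". No covariate is named there, and the choice between ANOVA and mixed model is left open.

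The Study outcomes section sets the measurement times: "At baseline, 1 week after and 3 months after the (group or individual) visit participants will be asked to fill out a questionnaire". The secondary scales at issue are fear of cancer ("The Cancer Worry Scale will be used to assess the fear of cancer") and quality of life ("The quality of life will be measured by the EORTC-Q30 and the EORTC-BR23"). Both are continuous scores, so on that schedule each has one baseline and two follow-up values.

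**The concern.** With three waves and no covariate, the ordinary form of a repeated-measures ANOVA takes all three scores as outcomes and tests group by time. A mixed model that lets the baseline means differ between the arms does the same. In either case the contrast at 1 week or 3 months is the between-arm difference in raw change from baseline.

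In a randomised comparison this has two drawbacks. It is less precise than adjusting for baseline. It also subtracts the whole of any chance baseline difference D, where the adjusted analysis subtracts only ρD. Given the observed imbalance, it therefore over-corrects by (1−ρ)D.

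This matters most for fear of cancer, because the abstract warns that "it should be noted that group sessions may increase fear in some patients or influence their decision making". The Cancer Worry Scale is the instrument assigned to that fear, and a less precise test makes a real rise easier to miss.

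**Working it through.** **Stated figures.** The article gives no sample size, power or precision for any secondary outcome, so there is no figure of its own to reproduce here. Its only sample-size figure is 80 per group for the SCL-90. The two-sided two-sample formula with the stated inputs (difference 13.5, SD 45, 5%, 80% power) gives 175 per group, or 206 after 15% drop-out. That mismatch is a separate matter and neither supports nor weakens this point.

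**Inputs.**
- Allocation 1:1 (abstract).
- Evaluable women per arm: 80 × (1 − 0.15) = 68 (Power calculations section).
- Illustrative standardised difference: 13.5/45 = 0.3. This is the SCL-90 target; the article gives none for the secondary scales.
- ρ, the correlation between baseline and follow-up score: not given, so a range is shown.

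**Formulas.** With equal variances at each wave, in SD² units per woman:
- raw change: V = 2(1−ρ)
- baseline-adjusted: V = 1−ρ²
- ratio: 2(1−ρ)/(1−ρ²) = 2/(1+ρ)
- approximate two-sided 5% power at one wave: Φ(0.3/√(2V/68) − 1.96)

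**Results.**

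| ρ (assumed) | V, raw change | V, adjusted | Variance ratio | SE ratio | Power, raw change | Power, adjusted |
|---|---|---|---|---|---|---|
| 0.3 | 1.40 | 0.91 | 1.54 | 1.240 | 31.5% | 45.0% |
| 0.5 | 1.00 | 0.75 | 1.33 | 1.155 | 41.7% | 52.4% |
| 0.6 | 0.80 | 0.64 | 1.25 | 1.118 | 49.8% | 59.0% |
| 0.7 | 0.60 | 0.51 | 1.18 | 1.085 | 61.7% | 68.8% |
| 0.8 | 0.40 | 0.36 | 1.11 | 1.054 | 79.0% | 83.0% |
| 0.9 | 0.20 | 0.19 | 1.05 | 1.026 | 97.5% | 98.0% |

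Example at ρ = 0.5. Raw change: 0.3/√(2 × 1.00/68) = 1.749, and Φ(1.749 − 1.96) = 41.7%. Adjusted: 0.3/√(2 × 0.75/68) = 2.020, and Φ(2.020 − 1.96) = 52.4%. At this ρ, raw change does no better than ignoring baseline altogether, since the follow-up score alone has V = 1.

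**Check on the model form.** Generalised least squares on three waves (68 per arm, compound symmetry assumed) gives the ratios in the table when the baseline means are free in each arm. With a common baseline mean the ratio is 1.00 at every ρ. The loss therefore comes from leaving the baseline means free, not from having baseline in the response vector.

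The power columns are illustrative, because they borrow the SCL-90 effect size and ignore any clustering within group sessions.

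**The case against.** The strongest reply is that the sentence does not say what role baseline plays. It mentions no change score, no group-by-time contrast and no free baseline means. The same section applies the language of trends to the baseline-adjusted method as well: "In addition ANCOVA provides the opportunity to compare trends over time between the two groups". That phrase alone therefore cannot show that baseline is an outcome wave. A mixed model on the follow-up scores with baseline as covariate also fits the sentence. In addition, a condensed article may leave such detail to a fuller document.

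Much of this stands. A reader might infer that the plan definitely tests raw change on the secondary scales; the article does not say so, and one of its two named options can avoid the loss entirely. A reader might also infer bias or a false type I error rate. Neither follows, because the change comparison is unbiased over randomisation. Nor is it a contradiction to give secondary outcomes a different model from the primary one. The concern about harm is also partly met elsewhere, since psychological distress is a primary outcome and its SCL-90 model is baseline-adjusted.

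What remains is that the article does name methods. It gives the SCL-90 analysis a baseline covariate, then offers ANOVA for the secondary outcomes with none. The usual meaning of that option, on a three-wave schedule, is the less precise analysis. The point concerns an option the text permits, not an omission.

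**Conclusion.** The concern holds in a conditional form. For the Cancer Worry Scale and the EORTC scales, the plan permits an analysis that is valid but less precise than one available from the same data. If the ANOVA option or a mixed model with free baseline means is used, the excess variance at a single wave is about 33% at ρ = 0.5, 18% at 0.7 and 11% at 0.8. If a mixed model with a baseline covariate or a common baseline mean is used, the loss is nil.

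These sizes rest on an assumed ρ and on equal variances across waves. Measurements only about two weeks apart (one week before and one week after the visit) may well correlate highly, which would put the 1-week loss towards the lower end. A reader might take the power columns as a forecast for the trial, but the article sets no effect size or power target for these scales. No stated figure and no primary conclusion depends on the point. It is an inexpensive gain in efficiency, not a failure of validity.

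**What to change.** In the Statistical analysis section, for the continuous secondary scales with a baseline value (Cancer Worry Scale, EORTC scales), replace the open choice with one stated model. This is a mixed model with the 1-week and 3-month scores as outcomes, and group, time, group-by-time and the scale's own baseline score as covariate. A three-wave mixed model with baseline means constrained equal across arms serves equally well. Report the adjusted group difference at each wave.

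Both forms presume a baseline score that is unaffected by knowledge of the allocation. The abstract places the baseline questionnaire one week before the visit, and the Recruitment and randomization section allocates women for their next visit once consent is given. The sponsor should therefore confirm that baseline is completed before allocation is known.

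The cost is one sentence of analysis wording, with no extra patients, visits or data. If the sponsor already intends this model, the sentence simply removes the ambiguity.
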